### Analytic strategy

To achieve the three main objectives of this study, several retrospective and forecasting methods will be integrated. The detailed steps of each objective are described below. As discussed before, the Aim 1 is to use very large datasets to evaluate the effect of a broad range of socioeconomic determinants on incidence, treatment adherence, hospitalization, case fatality and mortality from HIV/AIDS. A hierarchical framework to investigate the social determinants of HIV/AIDS [40, 48] will be developed. Social indicators will be grouped into three blocks representing distal, intermediate, and proximal variables. Distal variables are related to geographical factors and include region and location of the family household (urban or rural). Intermediate variables are related to socioeconomic position in the community and include self-identified race or ethnicity, education, employment, and *per capita* family income. Proximal variables are related to household conditions at the family level and include building material, water supply, sanitation, electricity, waste disposal destination, and household density. Following a hierarchical analytical approach, three adjusted Poisson regression models will be used with cluster-robust standard errors (SEs) [49–51], i.e., accounting for familial clustering of covariates, to estimate the adjusted incidence rate ratios (IRRs) of morbidity or mortality HIV/AIDS outcomes. All variables associated with Incidence Rate Ratio of the outcomes at a significance threshold of p-value less than 0.10 will be included in the next level model. Model 1 will include distal factors plus age and sex. Model 2 will include variables from model 1 and intermediated factors. Model 3 will include variables from model 2 and proximal factors.

The second aim of this study is to assess the impact of the Bolsa Familia Program exposure and Primary Health Care coverage on incidence, treatment adherence, hospitalization, case fatality, and mortality from HIV/AIDS, evaluating their impact, alone and in a synergistic fashion, on a broad range of subpopulations. To achieve this goal, the following steps will be performed:
**Step 1**. To analyze the differential impact and dose-response of BFP according to the duration of the intervention, amount of money received and compliance with conditionalities. The retrospective impact evaluation will use arguably one of the most robust study designs for causal inference in quasi-experimental studies: the regression discontinuity design (RDD), which allows a quasi-randomization of the subjects under study around the eligibility threshold [52, 53]. The eligibility of the BFP is determined by two thresholds: one for poor families (below 154 BRL *per capita*) with vulnerable members (children or pregnant women), the second for extremely poor families (below 77 BRL *per capita*), even without any vulnerable member. BFP is one of the most accurately targeted CCTs, and if inclusion/exclusion errors are identified, a fuzzy-instead of sharp-RDD will be used. The presence of two different cut-offs will allow to evaluate the different impact of the BFP on the two different thresholds: between eligible and non-eligible poor and eligible and non-eligible extremely poor families. In order to explore the impact in subjects outside of the RDD selected bandwidth, analyses using Random Administrative Delays (RAD) and Propensity Score Matching (PSM) [54–56] will also performed. These methods have been already used for similar studies with the CadUnico to evaluate the effects of BFP on Tuberculosis (TB). The PSM has also been used in with the same linked dataset to complementarily evaluate the impact of BFP on TB cure and mortality rate [21]. Where possible, combination of these designs—such as the PSM-RDD—will be used [57]. The complementary use of the three methods will consequently allow to assess the effects of BFP along the complete range of socioeconomic conditions represented over the 100 million individuals of the dataset. All analyses above will be stratified according to the years of exposure to BFP and amount of received money over the 12 years of follow-up, to evaluate a dose-response relation with the duration and intensity of support received. Analyses will also explore lagged effects by associating exposures of previous years with outcomes of a range of following years.**Step 2**. To measure the BFP impact on a broad and detailed range of different subpopulations defined by individual demographic and socioeconomic characteristics and by local geographic regions, and municipality development. The evaluation designs and methods described above will be used for stratified analyses with each subpopulation of interest: age groups, gender, illiteracy and educational level. Further stratifications will be based on the characteristics of the municipality: human development index, GDP per capita and Gini index of income inequality.**Step 3**. To analyze the dose-response of FHS according to the extent and duration of the municipal coverage. Using the same structured dataset from the previous analyses of Aim 2, and considering that coverage of FHS is only available at the municipal level, the FHS impact will be evaluated using a Propensity Score (PS) weighted multilevel negative binomial regression design with individual level-variables from Aim 1, including BFP as adjusting variable [56]. To avoid ecologic fallacy, the dataset will be resized and limited to municipalities with 90–100% (consolidated FHS coverage = exposed) and 0–10% FHS coverage (low/insignificant FHS coverage = control) in the study period. The intervals 0–10% and 90–100%, instead of 0% and 100%, will be used to consider uncertainty in the coverage measure, but sensitivity analyses will be performed with 0% and 100%.**Step 4**. To measure the FHS impact on a broad range of different subpopulations defined by individual demographic and socioeconomic characteristics and by local geographic regions. As in the Step 2 of the Aim 2, the evaluation designs and methods will be used for each subpopulations of interest: age groups, gender, illiteracy and educational level. Moreover, further stratifications also will be based on the characteristics of the municipality.**Step 5**. To evaluate the synergistic individual-level exposure to BFP with municipal-level coverage of FHS on incidence and mortality from HIV/AIDS. Using the same multilevel and multivariable regression models above, the interaction effects of BFP with FHS will be evaluated with product terms and stratification analyses.

The main limitation of Aim 1 and Aim 2 is the usage of the population registered in the CadUnico that will be used rather than the overall Brazilian population to evaluate the impact of the interventions under study. While for the evaluation of the BFP the use of a control group which is part of the poorest half of the Brazilian population—instead of the overall population—is supposed not to influence the impact estimates of RDD and PSM designs (which uses controls comparable to the exposed), for FHS this is not necessarily the case. While the use of PS weighted regression will be able to weight observations and allow an unbiased estimation of the FHS effects (in relation to implementation bias), we assume that the FHS effect in the upper income group of the CadUnico—which includes a great part of the Brazilian middle-class—will not be significantly different from the richest half of the Brazilian population not included in the CadUnico dataset. All analyses for Aims 1 and 2 will be performed with STATA 16^®^ and R Studio 3.6^®^.

Finally, to achieve Aim 3, some steps are needed to be developed. This objective is to forecast HIV/AIDS incidence, prevalence and mortality scenarios, using the broad range of subpopulations estimates and parameters from the retrospective analyses, according to socioeconomic changes and coverage intervention scenarios up to 2030. Leveraging the richness and granularity of parameters obtained from Aim 1 and 2, mathematical models will fully explore and comprehensively evaluate the effect of several scenarios using compartmental models, microsimulation, and agent-based models. The steps are described below.
**Step 1**. To evaluate the most adequate compartmental structure for the mathematical models. In the first exploratory stage we will use compartmental models (CM) to evaluate which structures and compartments are more adequate to represent the influence of the wide range of social determinants, the effects of BFP and FHS on incidence, prevalence, compliance to treatment in the HIV/AIDS epidemic in Brazil as a whole.**Step 2**. To develop an Agent-Based Model (ABM) to evaluate the effect of interactions in HIV/AIDS dynamics. ABM will be used to explore patterns of interactions between individuals [58]. ABM focuses on understanding population dynamics, and models individuals who “choose” actions under the conditions and environment where they are situated. ABM are increasingly used in public health [59–61] and in HIV/AIDS studies [62–65].**Step 3**. Develop an integrated Microsimulation, Compartmental and Agent-Based Model (MS-CM-ABM) and forecast the impact of alternative economic and policy scenarios on HIV/AIDS outcomes. The third stage of modelling of the Aim 3 will integrate the two analyses above with microsimulation (MS), creating an integrated and comprehensive model. MS-CM-ABM can provide more accurate estimates of policy effects than traditional compartmental models or time-series forecasting models, which use only the average values in the population. Both MS and ABM use the micro-level description to represent the real phenomena, but while ABM is focused on the understanding the interaction dynamics in relatively small population, MS is used to recreate large synthetic populations from retrospective datasets. Their integration can be particularly useful—as in our case—when both the heterogeneity and dynamic interactions of the population are relevant for the outcome under study. A representation of the proposed MS-CM-ABM model is presented in Fig 3. Despite the growing interest in the integration of the two approaches, few studies have employed this novel approach [66–68].

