**Aim 1**To integrate aggregate and individual-level large datasets to evaluate the effect of a broad range of socioeconomic determinants on incidence, treatment adherence, hospitalization, case fatality and mortality rates from HIV/AIDS;**Aim 2**To assess the impact of BFP exposure and FHS coverage on incidence, treatment adherence, hospitalizations, case-fatality, and mortality from HIV/AIDS, evaluating their individual and synergistic effects on a broad range of subpopulations;**Aim 3**To forecast HIV/AIDS incidence, prevalence and mortality scenarios in Brazil using integrated microsimulation (MS), compartmental model (CM) and agent-based models (ABM) that leverages the large set of results from Aims 1 and 2, to explore the impact of different socioeconomic and policy scenarios on HIV/AIDS morbidity and mortality up to 2030.

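### Aim 1 clusters standard errors on the family only, so those for region (and any municipality-level covariate used) are too small by an amount the protocol does not let us determine

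*Protocol article*

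**What the plan says.** The Aim 1 paragraph of Analytic strategy describes three nested Poisson models that estimate incidence rate ratios with cluster-robust standard errors. It then says what the clustering means: "accounting for familial clustering of covariates". No municipal cluster, random effect or other geographic dependence term is named for Aim 1.

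The covariates enter in blocks. "Model 1 will include distal factors plus age and sex", and the distal factors are region and whether the household is urban or rural. Individual socioeconomic variables follow in Model 2 and household conditions in Model 3. Variables associated with the outcome "at a significance threshold of p-value less than 0.10 will be included in the next level model".

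Two other places bear on the point. The aims in the Introduction say that Aim 1 will "integrate aggregate and individual-level large datasets". In Aim 2, Step 3, the effect of Family Health Strategy coverage, which is available only by municipality, is to be estimated with a "Propensity Score (PS) weighted multilevel negative binomial regression design".

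**The concern.** A family-clustered variance allows relatives to be correlated but treats different families as independent, including families in the same municipality. For a covariate that varies between members or between neighbouring families, this may do little harm. Region does not vary within a municipality. Whatever pushes a municipality's rate up or down after adjustment (local transmission, testing, notification or services, for example) is shared by all its families and does not average out as families are added. A family-clustered standard error leaves that component out, so for region the bias is downward whenever such residual variation exists.

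Two things rest on the affected quantities: the reported intervals and p-values for region, and the p<0.10 test that decides whether region is carried into Models 2 and 3. The plan uses a multilevel model for a municipal exposure in Aim 2 but does not apply that reasoning to region in Aim 1.

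**Working it through.** The protocol states no standard error, intracluster correlation, design effect or power for Aim 1, so there is no figure to reproduce. The check asks how far a family-only standard error could be off.

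**Inputs from the protocol**
- Cluster unit: family. Region is in Model 1. Carry-forward threshold 0.10 (taken as two-sided; the protocol does not say). All from Analytic strategy.
- A rough upper scale for events: 835,791 notified AIDS cases (Introduction) × about 50% of the population in the registry (Data and measures) ≈ 418,000. Events in the linked cohort are not given.

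**Assumed inputs, not in the protocol**
- 5,500 municipalities.
- 20,000, 100,000 or 400,000 events, because Aim 1 has several outcomes.
- Residual between-municipality coefficient of variation of the rate, c, from 0.05 to 0.5.

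**Formula, municipalities of equal size.** For a covariate constant within municipality, with μ events per municipality:

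variance inflation = 1 + μc²; true type I error = 2[1 − Φ(1.645 / √inflation)].

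- 400,000 events: μ = 400,000 / 5,500 = 72.7. At c = 0.3, inflation = 1 + 72.7 × 0.09 = 7.5, standard error factor 2.75, type I error 0.55.
- 20,000 events: μ = 3.6. At c = 0.05, inflation = 1 + 3.6 × 0.0025 = 1.01, factor 1.00, type I error 0.10.

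**Simulation, municipalities of unequal size.** There were 1,000 replicates per setting, with a log-normal municipal effect, municipality sizes with log-SD 1 and an assumed family design effect of 1.05. Each cell gives, for a two-region contrast, the ratio of the municipality-clustered to the family-only standard error, then the true type I error of the family-only test at nominal 0.10.

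| c | 20,000 events | 100,000 events | 400,000 events |
|---|---|---|---|
| 0.05 | 1.01; 0.11 | 1.06; 0.13 | 1.21; 0.19 |
| 0.1 | 1.04; 0.11 | 1.21; 0.20 | 1.69; 0.31 |
| 0.2 | 1.17; 0.19 | 1.70; 0.33 | 2.90; 0.60 |
| 0.3 | 1.35; 0.24 | 2.27; 0.48 | 4.19; 0.70 |
| 0.5 | 1.83; 0.39 | 3.54; 0.65 | 6.89; 0.80 |

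These exceed the equal-size results because large municipalities dominate. If sizes are log-normal with log-SD 1, μ is multiplied by e = 2.718. At c = 0.5 and 400,000 events this gives (1.05 + 0.25 × 72.7 × 2.718) / 1.05 = 48, with square root 6.9, in line with the simulated 6.89. The simulation error of a true 0.10 is √(0.1 × 0.9 / 1,000) ≈ 0.009, so 0.11 at the mild end cannot be told apart from nominal.

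**Urban/rural.** Under the same settings the factor is 1.00 to 1.17 at 20,000 events (type I error 0.09 to 0.18) and 1.03 to 2.86 at 400,000 events (0.10 to 0.57).

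**Fewer municipalities.** With 2,000 municipalities, 100,000 events and c = 0.3, the factor for region is 3.51 (type I error 0.64). With 500 municipalities, 20,000 events and c = 0.1, it is 1.40 (0.24).

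**After clustering on municipality.** Simulated type I error at nominal 0.10 is about 0.09 to 0.12 in every setting, for both variables.

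**The case against.** The strongest case on the other side is that the problem touches little of what Aim 1 is about. Of the covariates listed, only region must be constant within a municipality. Urban or rural location is recorded per household, and the education, income, employment and housing variables are individual or household measures. That stands: nothing here shows that their standard errors are materially wrong.

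Four stronger readings are tempting, and the protocol does not support them.

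- *The intervals are far too narrow.* A reader might pick 20 to 70 events per municipality and c of 0.3 to 0.5, and obtain inflation of 1 + 0.09 × 20 = 2.8 to 1 + 0.25 × 70 = 18.5, with 95% interval coverage of 76% down to 35%. The arithmetic is right, but the inputs are assumed and leave out the range in which almost nothing happens. The relevant c is what remains after adjustment, and the protocol gives no value for it.
- *Municipal covariates in Aim 1 are already affected.* The aims mention aggregate data, but the Aim 1 models list no municipal aggregate variable. The point applies to one only if it is used.
- *The forecast intervals inherit the false precision.* The Aim 3 text lets parameters vary by their retrospectively measured distributions over 10,000 simulations, but does not name the region coefficient as an input. Forecasts are affected only if such coefficients feed those models.
- *Aim 2 has the same fault.* Step 3 already uses a multilevel model, and the article states no variance estimator for the regression discontinuity, administrative delay or propensity score analyses. No case is made here about them.

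It is also fair to say that a region test which passes too easily mainly keeps a geographic adjuster in Models 2 and 3; no bias in any rate ratio has been shown. None of this justifies family-only clustering for region itself, and since the cluster unit is stated, this is not a detail left to a fuller analysis plan.

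**Conclusion.** The point holds for region and, conditionally, for any municipality-level covariate used in Aim 1; it holds in weaker form for urban/rural location. The direction is certain once rates vary between municipalities beyond the modelled covariates. The size is not: under the assumed ranges above, with 5,500 municipalities, it runs from negligible (a rare outcome with little residual variation) to a standard error about seven times too small (a common outcome with c = 0.5). The change should be made because the rule as written is wrong for a covariate it is applied to and the correction is cheap, not because severe error has been demonstrated.

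**What to change.** In all Aim 1 models, replace family by municipality of residence at cohort entry as the cluster for the robust standard errors, and apply the p<0.10 rule to the resulting p-values. Where families are nested in municipalities, this also covers correlation within families. Municipality of residence is already one of the linkage variables (Data and measures).

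The cost is a changed cluster variable in the Stata or R call. Rate ratios are unchanged for a given set of covariates, although that set may differ if region no longer passes the threshold. Intervals for geographic covariates become wider.

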**Methods and analysis:**

We will combine individual-level data from all national HIV/AIDS registries with large-scale databases, including the “100 Million Brazilian Cohort”, over a 19-year period (2000–2018). Several approaches will be used for the retrospective quasi-experimental impact evaluations, such as Regression Discontinuity Design (RDD), Random Administrative Delays (RAD) and Propensity Score Matching (PSM), combined with multivariable Poisson regressions for cohort analyses. Moreover, we will explore in depth lagged and long-term effects of changes in living conditions and in exposures to BFP and FHS. We will also investigate the effects of the interventions in a wide range of subpopulations. Finally, we will integrate such retrospective analyses with microsimulation, compartmental and agent-based models to forecast future HIV/AIDS scenarios.

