The Brazilian conditional cash transfer (CCT) program, Bolsa Familia Program (BFP), is the world`s largest CCT and targets poor households earning between US$18–36 per person per month. Eligibility is assessed at the federal level to minimize errors and fraud. The monthly cash benefits range from US$17 to a maximum of US$41 (depending on household size and composition) and payments are credited directly to a beneficiary debit card [17, 18]. Conditions for receipt of the benefits include: attendance at prenatal and postnatal monitoring sessions; children aged 0–7 must be up-to-date with nutrition monitoring and immunizations, and children must attend school. Previous studies have assessed the effectiveness of the BFP on child morbidity and mortality and a host of other conditions, from suicide and tuberculosis to leprosy [19–23]. Brazil has also implemented over the last two decades one of the most consolidated and evaluated Primary Health Care (PHC) programs, the Family Health Strategy (FHS), in a comprehensive approach to providing PHC as part of Brazil’s National Health Services, the Unified Health System (SUS) [24]. These facilities are open to all Brazilian citizens and are located within community settings close to where people live. Several studies have evaluated FHS effectiveness, demonstrating that expansion of the FHS has contributed to better health outcomes, including reducing infant and adult mortality, decreasing unnecessary hospitalizations, enhancing health system functions such as recording of vital statistics, and decreased inequities in both healthcare access and health outcomes [25–32].

Brazil is also an extremely data-rich country, where demographic, socioeconomic and interventions coverage data are available in terms of both quantity and adequate quality. Several impact evaluations of CCT have been performed using publicly available secondary aggregate-level longitudinal data and, more recently, individual-level data using the 100 Million Brazilian Cohort [33]. For these reasons Brazil provides a unique opportunity to study the effects of changes in socioeconomic determinants, CCT and PHC on a such complex and chronic infectious disease as HIV/AIDS in LMIC. Therefore, the detailed objectives of the proposed study are described as follows:

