### Innovation of the study

This study breaks new ground by providing a unique opportunity to use unprecedented big longitudinal dataset of linked socioeconomic and health data to assess the effects of socioeconomic conditions, PHC and CCT on all sequential outcomes of HIV/AIDS morbidity and mortality. Moreover, this study provides the unique opportunity to assess potential effect modification and synergistic effects of the simultaneous receipt of CCT and PHC, and how baseline socioeconomic conditions influence the effectiveness of both types of programs on the burden of HIV/AIDS. The longitudinal aspect of the cohort, which has a long follow-up period of 18 years of socioeconomic and health data, will allow us to explore and assess in-depth dynamics, lagged and long-term effects of changes in living conditions and in exposures to BFP and PHC. One of the study’s most relevant potential contribution to translational science will be the systematic integration of the large dataset and results from the retrospective impact evaluations with the prospective mathematical models, developing more reliable forecast scenarios than models which use parameters from other studies or populations. Moreover, the creation of a pioneering hybrid microsimulation, compartment and agent-based model (MS-CM-ABM), which will be supported by the very large number of parameters available from the retrospective big data evaluation, will be an innovation in the epidemiology of infectious diseases, and will be essential to the effort of modelling the effects of social determinants, CCT and PHC on HIV/AIDS. To date, very few studies in HIV/AIDS have introduced poverty and CCT as variables in their predictive models, and they have not explored their influence in depth [34, 35]. Regarding PHC, no models have assessed the impact of access to universal PHC on HIV/AIDS-relevant outcomes (beyond universal HIV screening in primary care settings) [36], neither have mathematical models been developed to estimate these effects.

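### Stratifying every BFP analysis by years and money received during follow-up builds immortal time into the terminal outcomes and gives up the threshold comparison in the RDD

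*Protocol article*

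**What the plan says.** The rule is in the Protocol article, Analytic strategy, Aim 2, Step 1: "All analyses above will be stratified according to the years of exposure to BFP and amount of received money". The dose window follows directly: "over the 12 years of follow-up, to evaluate a dose-response relation". The rule comes after the descriptions of the RDD, the Random Administrative Delays design (RAD) and Propensity Score Matching (PSM), so it covers all three.

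Other statements bear on it:

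- The aim is causal: "to evaluate a dose-response relation with the duration and intensity of support received".
- The RDD is justified because it "allows a quasi-randomization of the subjects under study around the eligibility threshold". A fuzzy version is foreseen if targeting errors are found.
- The outcomes listed for Aim 2 include case fatality and mortality, which end follow-up, as well as incidence, hospitalization and treatment adherence.
- Lagged effects will also be explored, as an addition to the stratified analyses.
- Data and measures says that CadUnico holds the timing and monthly amount of BFP payments. The Introduction puts the monthly benefit between US$17 and US$41, varying with the size and make-up of the household.
- Innovation of the study says the cohort "has a long follow-up period of 18 years". The Abstract describes data "over a 19-year period", 2000 to 2018.

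**The concern.** The dose that defines the strata accrues during the follow-up in which events are counted. Someone who dies in year 4 cannot enter a stratum of more than 9 years, and everyone in that stratum survived at least 9 years. Those years carry person-time but could not have carried an event. The comparison can then show a gradient that BFP did not cause.

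The second difficulty is specific to the quasi-experimental designs. Being just below or just above the income threshold is close to random. How long a family stays in the programme and how much it collects are not. Both are settled after the threshold has acted, and both differ by side of it. Conditioning on them gives up the feature for which the RDD was chosen.

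At stake is the dose-response result of Aim 2 Step 1. In a cohort of this size, a spurious gradient would come with narrow intervals.

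**Working it through.** The article gives no event rate, uptake, discontinuation rate or sample size, so there is no figure of its own to reproduce. From it come the 12-year window, the outcomes and the stratification rule. Everything else below is assumed.

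**1. Bound for the top stratum.** Assume a constant event rate r per person-year, no BFP effect, and receipt and follow-up that stop at the event. A person with more than 9 years received passes the 9-year mark at year 9 or later, so at most 3 years remain in which an event can occur. In the most favourable case (receipt from time zero):

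- expected person-time after year 9: x = (1 − e^(−3r))/r, which is at most 3
- observed rate divided by true rate: x/(9 + x)

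As r tends to 0 this is 3/12 = 0.25. At r = 0.02, x = 2.912 and the ratio is 2.912/11.912 = 0.244. At r = 0.10, x = 2.592 and the ratio is 2.592/11.592 = 0.224. The bound needs no assumption about uptake or exit patterns.

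**2. Simulation under no effect.** Assumed: 2,000,000 people, 60% ever recipients, start uniform over years 0–6, 10% per year discontinuation, receipt and follow-up stopping at the event. Rate ratios against zero years received:

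| Event rate per person-year | 0–3 y | 3–6 y | 6–9 y | >9 y |
|---|---|---|---|---|
| 0.0003 | 1.06 | 0.86 | 0.22 | 0.07 |
| 0.02 | 1.01 | 0.79 | 0.23 | 0.09 |
| 0.10 | 0.82 | 0.55 | 0.21 | 0.09 |

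The top-stratum ratios fall below the bound partly because the reference is inflated: people with an event before their first payment are classed as zero dose. At 0.02 the zero-dose rate is 1.38 times the true rate and the >9-year rate is 0.127 times it, so the ratio is 0.127/1.38 = 0.09.

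**3. Sensitivity to uptake and exit.** A second set-up had 50 events per 100,000 person-years, 10% per year exit, and half of recipients starting at baseline. It gave 0.76, 0.63, 0.53 and 0.16. With 5–20% exit or a fourfold event rate, the >9-year ratio stayed at 0.16–0.17. Further runs varying late-start timing and exit gave 0.73 to 2.11 for 0–3 years, 0.58 to 1.91 for 3–6 years, and 0.17 to 0.19 for more than 9 years. The top stratum is stable; the low-dose strata can fall on either side of 1.

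**4. Person-time split by dose accrued to date.** For 0, <3, 3–6, 6–9 and >9 years, the ratio to the true rate is 1.00, 0.99, 1.00, 1.01 and 1.07 at 0.02 per year, and 1.00, 1.00, 1.00, 1.00 and 1.01 at 0.05. At rates of 0.005 and below, the last stratum scatters (0.85 on 290 events, 1.21 on 26). A repeat of that stratum with 20,000,000 people gave 1.00 at 0.005, 0.02 and 0.05. The distortion therefore comes from the stratification.

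**5. Non-terminal outcomes.** With receipt counted to year 12 regardless of the event, all strata gave 1.00.

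**6. RDD.** Under a sharp design every ineligible family has zero dose, so no positive-dose stratum has families on both sides of the threshold. For a fuzzy design, assume 85% take-up among eligible and 10% among ineligible, 0.02 events per year with frailty, and no effect. Each positive-dose stratum then holds only 1.6% to 2.9% of ineligible people. The unstratified contrast is 1.00. Eligible people by years received against all ineligible give 2.42 (0 years), 1.38 (0–3), 1.07 (3–6), 0.31 (6–9) and 0.12 (>9).

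In that model uptake and exit do not depend on risk, so these departures are immortal time carried into the RDD. Repeating it with dose not cut off at the event gave 1.00 to 1.01 throughout. The loss of quasi-randomization is therefore a design argument: nothing in the article makes years or amount received independent of risk.

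**7. Follow-up length.** 2018 − 2000 = 18 elapsed years, or 19 calendar years counted inclusively. These two agree. The 12-year window has no stated start or end.

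**The case against.** The strongest reply is that the article never says total dose. Its wording could also describe person-time classified by dose to date, and exposure coding is often left to a fuller document. The payments are dated, Poisson cohort models are planned, and lagged analyses are mentioned. If the full plan splits person-time, the immortal-time problem disappears. This stands as a condition. But the rule as printed, "amount of received money over the 12 years of follow-up", sums dose over the outcome window, nothing makes it time-updated or landmarked, and the lagged analyses are an extra. The RDD point survives either coding.

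Four stronger readings are tempting, and the article does not support them:

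- **A protective gradient must appear whatever the truth.** It need not for hospitalization or adherence if receipt is counted regardless of the event, and low-dose strata can look harmful.
- **All three designs fail alike.** In RAD, the delay itself creates differences in duration, and that is the design's own variation. Only duration driven by exit is suspect. Dose strata in an RDD could share a zero-dose control group, but that is no longer the threshold contrast. Fuzzy RDD handles imperfect take-up; it does not justify stratifying on dose received. Household composition is recorded and available for matching, so its link with the amount paid is not by itself an unhandled defect.
- **The bias flows into the Aim 3 forecasts.** Aim 3 uses subpopulation-specific estimates and other retrospective parameters, with scenarios on coverage. Nowhere does the article say that duration- or amount-specific estimates enter.
- **Follow-up is given in three conflicting lengths.** Only the 12 years is unexplained.

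**Conclusion.** The concern holds for the rule as written, within these limits.

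For mortality, case fatality and first-event analyses in which receipt and person-time stop at the event, a stratum with more than 9 of 12 years received shows at most 25% of the true rate when BFP has no effect. This rests on a constant event rate and on dose being summed over follow-up. The simulated ratios against zero dose, 0.07 to 0.19 across the set-ups tried, also depend on assumed uptake and exit. No direction or size can be claimed for low-dose strata.

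For the RDD, stratifying on realised years or amount abandons the comparison that gives the design its validity, however dose is coded. The size of any resulting bias cannot be derived from the article. In RAD the criticism is confined to exit-driven duration.

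Because the article fixes the rule explicitly for all BFP analyses, it should be replaced before the analyses are run.

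**What to change.** Replace the stratification rule in Aim 2, Step 1:

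1. **PSM and Poisson cohort analyses.** Split person-time by period and enter cumulative years and cumulative per-capita amount as time-updated, lagged covariates. Alternatively, use landmark strata whose exposure window closes before outcome counting begins. Either way, each event is set against exposure accrued before it.
2. **RDD and RAD.** Keep the threshold or delay contrast for all families at fixed horizons since baseline (for example 1–3, 4–6 and 7 or more years). Let dose enter only as the instrumented variable in a fuzzy RDD, never as a stratifier.
3. **Dose window.** Give the start and end of the 12 years and reconcile them with the 2000–2018 period described elsewhere as 18 or 19 years.

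If the full plan already splits person-time by dose to date, saying so settles the immortal-time part; the RDD part still needs changing. The cost is revised analysis wording, a person-period data layout and more computing time. No new data are needed, because CadUnico already holds the dates and monthly amounts.
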